**Fig. 2 Fig2:**
[figure not shown]
Standard Protocol Items: Recommendations for Interventional Trials (SPIRIT) schedule of the trial. This is a randomized controlled trial which includes a 2-day baseline period and one acupuncture treatment. In the baseline period, recruited patients will be screened according to the inclusion criteria and exclusion criteria; then, eligible GSD patients will give informed consent and receive a physical examination. After allocation, the patients will receive once GB34 acupuncture, EX-LE6 acupuncture, or non-acupoint. The outcome assessments and fMRI scans are performed at baseline and at the end of acupuncture. In addition, a physical examination will be performed at the baseline. Adverse events will be recorded in the CRFs at any time during treatment. fMRI functional magnetic resonance imaging, SF-12 12-item Short Form Health Survey, NRS Numeric Rating Scale, SAS Self-rating Anxiety Scale, SDS Self-rating Depression Scale

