### Drop out criteria

(1) Quitting themselves during research; (2) not following the requirements; (3) having serious illnesses, complications, or adverse events during research; (4) showing emotional instability or having drunk coffee, strong tea, or alcohol before fMRI scan.

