### Ethical consideration

During the acupuncture treatment, some other interventions, such as symptomatic relief or psychopharmacological medications, are usually not allowed to use. However, if participants experience discomforts that are difficult to tolerate, they would be treated immediately. Researchers should record all relevant information into the CRFs. Participants in group C can choose to receive acupuncture treatment or health consultation for free after completing this trial.

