### Primary outcome measurement

The primary outcome will be measured by the NRS. NRS is a commonly used, validated, and reliable measure of the current self-reported pain intensity [46, 47]. NRS is a horizontal line with 10 segments, being labeled from 0 (no pain at all) to 10 (the worst pain imaginable). The NRS will be assessed at four timepoints: before and after the 1st task fMRI scan (before acupuncture), after acupuncture (before the 2nd task fMRI scan), and after the 2nd task fMRI scan.

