### Statistical analysis

#### Clinical data analysis

The clinical data will be statistically analyzed by SPSS 22.0 software (IBM SPSS Statistics, IBM Corp, Somers, New York). Skewed data distribution will be normalized. Means, standard deviations, and 95% confidence intervals (CIs) will be computed to describe continuous variables. Since only one session of acupuncture will be conducted in our study, the per-protocol (PP) analysis will be used, and the subjects with missing data will be excluded. The reasons for missing data should be recorded in detail.

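### The only analysis set stated for the NRS primary outcome is per-protocol complete cases, so the superiority comparison is open to selection bias whose size and direction the document cannot settle

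*Protocol article*

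**What the plan says.** The Clinical data analysis section fixes one analysis set: "the per-protocol (PP) analysis will be used, and the subjects with missing data will be excluded". Its stated reason is "Since only one session of acupuncture will be conducted in our study". Reasons for missing data are to be recorded. The article names no all-randomised analysis, no imputation and no missing-data sensitivity analysis.

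The rule covers the primary endpoint: "The primary outcome will be measured by the NRS", at four timepoints around one treatment and two scans. The Clinical outcome analysis section compares these scores by repeated-measures ANOVA, followed by one-sided planned contrasts of change.

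The Drop out criteria section lists quitting, then "not following the requirements; (3) having serious illnesses, complications, or adverse events during research", then "showing emotional instability or having drunk coffee, strong tea, or alcohol before fMRI scan". On timing, the legend to Fig. 2 says: "After allocation, the patients will receive once GB34 acupuncture, EX-LE6 acupuncture, or non-acupoint". The Sample size section allows for 10% dropout.

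**The concern.** The single-session argument answers only part of the problem. It makes incomplete treatment unlikely. It does not prevent a participant from withdrawing, breaking a requirement or having an adverse event once allocated, and it does not make such losses equal across arms.

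Three features of the design allow the losses to differ by arm. The Interventions section seeks deqi in groups A and B but does not require it in group C. The Blinding section leaves the acupuncturist unblinded. The Discussion concedes that complete blinding of participants is impossible. Whether a participant has failed to follow requirements is also partly a matter of judgement.

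Excluding every subject with missing data adds to this. A participant who lacks only the fourth NRS value loses all four, including the scores just before and just after needling.

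At stake is the main objective, a comparison of each acupoint with the non-acupoint. It rests on randomisation, which the only stated analysis set does not preserve, and no second analysis is planned that would show whether the exclusions mattered.

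**Working it through.** **Inputs from the Sample size section.** Expected NRS fall of 2.4 with GB34 or EX-LE6 and 0.85 with the non-acupoint, so the difference is 2.4 − 0.85 = 1.55. SD 2, α = 0.05, power 0.80, dropout 10%.

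**The plan's own figure.** Two-sided normal formula for two means: n = 2 × (1.960 + 0.842)² × 2² / 1.55² = 26.1, rounded up to 27 per arm. Then 3 × 27 = 81, and 81 / 0.9 = 90. Both stated totals are reproduced, so the fault lies in the analysis set and not in N.

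**When exclusions can occur.** Acupuncture follows allocation, so adverse events of needling, withdrawal after needling and failure to complete the second scan all come after randomisation. With 10% loss, 9 of 90 participants are left out, or 3 of 30 per arm if spread evenly.

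**Bias formula.** Let a fraction q of one arm be excluded, with a mean fall x points smaller than in those retained. The all-randomised mean fall is the retained mean minus q·x, so per-protocol overstates that arm's fall by q·x. The document does not give x, so the values below are assumptions, with q = 0.1.

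| Pattern of loss | x (points) | Bias in contrast | Share of 1.55 |
|---|---|---|---|
| Unrelated to arm and outcome | 0 | 0 | 0% |
| Both arms, same shift | any | 0 | 0% |
| One active arm only | 1 | 0.10 | 6% |
| One active arm only | 2 | 0.20 | 13% |
| One active arm only | 3 | 0.30 | 19% |
| One active arm only, no change in those lost | 2.4 | 0.24 | 15% |
| One active arm only, 2 points worse in those lost | 4.4 | 0.44 | 28% |

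The last two rows follow from (27 × 2.4 + 3 × 0)/30 = 2.16 and (27 × 2.4 + 3 × (−2))/30 = 1.96, each against a per-protocol 2.40. They are extreme: 2.4 and 4.4 points are 1.2 and 2.2 of the plan's SD.

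**Effect on false positives.** Suppose there is no true difference and only one active arm loses participants (27 against 30). SE = 2 × √(1/27 + 1/30) = 0.53. By the normal approximation, a bias of 0.1, 0.2 or 0.3 in favour of that arm turns a nominal 5% into 5.4%, 6.6% or 8.7% two-sided. One-sided, as in the planned contrasts, it becomes 7.3%, 10.2% or 14.0%.

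**Power with all randomised participants.** Two-sided, for a difference of 1.55, power is 85.1% at 30 per arm and 81.3% at 27. If the 10% who leave are counted as zero change (an assumption), the difference is 0.9 × 1.55 = 1.395 when this applies in both arms, with power 77.1%. It is 0.9 × 2.4 − 0.85 = 1.31 when it applies in the active arm only, with power 71.8%.

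**The case against.** The best defence is that this is a short experiment. One needling session sits between two scans, planned loss is only 10%, and much of that loss may have nothing to do with treatment. The cue task also runs before acupuncture, so intolerance of the first run cannot reflect response to needling. All of this stands, and it is why zero belongs in the range of bias. It does not rescue the rule: if exclusions are few and harmless, analysing everyone as allocated costs almost nothing, and if they are not harmless, the per-protocol result gives no warning.

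Nor is this a detail that a condensed article may leave to a fuller document. The article makes the choice and gives a reason for it.

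Three stronger readings go beyond the text.

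- A reader might infer that those removed are mostly those who did worst after needling. The Ethical consideration section says only that "if participants experience discomforts that are difficult to tolerate, they would be treated immediately" and that the information is recorded. It does not say that such a person is dropped or that the NRS is discarded. The article also does not say that the drop-out criteria define the per-protocol set. Outcome-related exclusion is possible, not shown.
- A reader might infer that the exclusions for emotional instability or for coffee, tea or alcohol act after allocation, and that the envelopes should be opened later. Figs. 1 and 2 are not available here, and the text does not say when allocation occurs relative to the first scan. The point does not rely on this.
- A reader might conclude that a per-protocol result cannot support any superiority claim. That is too absolute when loss may be small and unrelated to outcome.

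**Conclusion.** The point holds as a fault in a stated rule. Per-protocol complete cases is the only analysis set given for the primary outcome, the single-session reason does not justify it, and some of the listed exclusions can follow randomisation. The superiority comparison is therefore exposed to selection bias.

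The document fixes neither the size nor the direction of that bias. A moderate illustration is 0.1 to 0.3 points (6 to 19% of the planned difference), and a more extreme one is 0.24 to 0.44 points (15 to 28%). Both assume 10% loss confined to one active arm and worse outcomes in those lost. Loss mainly from the control arm, with the same kind of shift, would bias the contrast the other way.

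**What to change.** Rewrite the analysis-set paragraph in the Clinical data analysis section:

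- Primary NRS analysis: all randomised participants, in their allocated group, using every NRS value obtained. A mixed model for repeated measures over the four timepoints is one suitable choice, since a participant with a missing value still contributes the others.
- Data collection: continue to record the NRS after an adverse event or protocol deviation where possible.
- Sensitivity analysis: because a mixed model assumes that missingness is explained by observed data, add an analysis for data missing not at random, for example one that makes unobserved changes worse by a stated range in one arm and then in both.
- Per-protocol: keep as supportive, with exclusions and reasons reported by arm.

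The cost is a paragraph of wording and a little more analysis. No extra participants or visits are needed, and N = 90 can stay: power is about 85% for the planned difference if outcomes are collected on everyone. The price may be a less favourable estimate, and power falls to 77% or 72% if those who leave gain nothing, under the two assumptions worked above.

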#### Clinical outcome analysis

Comparison of NRS scores between four timepoints among three groups will be made using a repeated-measures ANOVA. Further, the planned contrast of changed NRS scores (before vs. after acupuncture; before vs. after fatty-food cues) will be conducted with a one-sided exact test for which *p* < 0.05 is considered significant.

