### Sample size

According to our previous study, the Numeric Rating Scale (NRS) of GSD patients decreased by 2.4 points after acupuncture and by 0.85 points after non-acupoint acupuncture. In this study, we anticipate a reduction of NRS score by 2.4 points after acupuncture with GB34 or EX-LE6, and we anticipate a reduction by 0.85 points after acupuncture with non-acupoint. With α = 0.05, 1 β = 0.8, and a standard deviation of 2, we need at least 81 participants in total. Considering a 10% dropout, the sample size of 30 in each group, with a total of 90 participants, would be required in this trial. And 30 patients in each group have a stable statistical power for brain functional network analysis [39].

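### Comparing unadjusted NRS changes is valid but less precise than adjusting for the pre-acupuncture NRS the trial already collects

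*Protocol article*

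**What the plan says.** Under Primary outcome measurement the article states: "The primary outcome will be measured by the NRS". The score is taken four times: "before and after the 1st task fMRI scan (before acupuncture), after acupuncture (before the 2nd task fMRI scan), and after the 2nd task fMRI scan". Two of the four readings therefore precede treatment, and the second of them is the immediate pre-acupuncture value.

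Under Clinical outcome analysis the method is fixed in two steps. The first is: "Comparison of NRS scores between four timepoints among three groups will be made using a repeated-measures ANOVA". The second is "the planned contrast of changed NRS scores (before vs. after acupuncture; before vs. after fatty-food cues"), which "will be conducted with a one-sided exact test for which" p < 0.05 counts as significant. Neither step names baseline NRS or any other variable as a covariate.

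The Sample size section also works with unadjusted reductions: "we anticipate a reduction of NRS score by 2.4 points after acupuncture with GB34 or EX-LE6", against 0.85 points for the non-acupoint, with an SD of 2.

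**The concern.** When a pre-treatment value of the outcome is available, a plain change score subtracts all of it. That is the most efficient use of the baseline only when the regression slope of post on pre, ρ × SD(post)/SD(pre), equals 1. For a pain score measured before and after a single session the slope is likely to be lower, and the change score then carries avoidable noise. The group-by-time term of a repeated-measures ANOVA is also a comparison of changes, so it does not recover the loss.

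What is at stake is precision. The sample size gives roughly 80% power for a two-sided comparison of two arms of 27, with little to spare. A variable already on the case report form could widen that margin without another patient, visit or scan.

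**Working it through.** **Inputs.** From Sample size: reductions 2.4 and 0.85, so a difference of 2.4 − 0.85 = 1.55; SD 2; α 0.05; power 0.80; 10% dropout. From Primary outcome measurement: two NRS readings before acupuncture and two after. Assumed, because the document does not give them: the pre/post correlation ρ (range 0.3 to 0.9), equal pre and post SDs, and SD 2 being the SD of the change score.

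**Step 1. Reproduce the plan's figure.** Two-sided, two-sample normal formula on unadjusted change:

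n = 2 × 2² × (1.960 + 0.842)² / 1.55² = 26.1, so 27 per arm; 3 × 27 = 81; 81 / 0.9 = 90.

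Both stated figures are reproduced. A one-sided calculation would give 21 per arm (63 in total), so 81 corresponds to a two-sided comparison of unadjusted change.

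**Step 2. Variance with and without adjustment.** With a common single-score SD of σ:

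- change score: 2σ²(1 − ρ)
- adjusted for baseline: σ²(1 − ρ²)
- ratio: (1 + ρ)/2, a reduction of (1 − ρ)/2

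**Step 3. Power at 27 per arm.** The adjusted SD is 2 × √((1 + ρ)/2). Power comes from the non-central t distribution, two-sided at 0.05, with one degree of freedom given up for the covariate.

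| ρ (assumed) | Variance reduction | SD | Power |
|---|---|---|---|
| unadjusted | – | 2.00 | 79.8% |
| 0.3 | 35% | 1.61 | 93.4% |
| 0.5 | 25% | 1.73 | 89.7% |
| 0.7 | 15% | 1.84 | 85.8% |
| 0.9 | 5% | 1.95 | 81.8% |

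**Step 4. The test as written.** The planned contrast is one-sided at 0.05. On that basis power is already about 88% unadjusted, and at ρ = 0.5 it rises to about 95%.

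**Step 5. Unequal SDs.** With k = SD(post)/SD(pre), the ratio of adjusted to change-score variance is k²(1 − ρ²) / (1 + k² − 2ρk). At ρ = 0.5:

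- k = 1.3: 1.2675 / 1.39 = 0.912, a reduction of about 9%
- k = 1.0: 0.75 / 1.00 = 0.75, a reduction of 25%
- k = 0.7: 0.3675 / 0.79 = 0.465, a reduction of about 53%

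**Step 6. SD 2 read as a single-score SD.** The section does not say which SD it means. On this reading (normal formula, two-sided, 27 per arm, equal SDs), change score against adjusted gives 67.2% and 84.7% at ρ = 0.3, 81.3% and 90.8% at ρ = 0.5, and 95.7% and 97.9% at ρ = 0.7. Adjustment is ahead at each of these values.

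**Step 7. Using all four readings.** If the mean of the two pre scores and the mean of the two post scores are used, under compound symmetry, the variance ratio is 0.73, 0.83, 0.91 and 0.97 at single-score ρ of 0.3, 0.5, 0.7 and 0.9. The gain is then 27%, 17%, 9% and 3%, smaller than in Step 3.

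**The case against.** The strongest reply is that nothing here is wrong. A comparison of changes is unbiased under randomisation, the sample size was built on the same quantity, and choice of covariates is often left to an analysis plan that is not shown. The first two statements stand, and they limit the point to lost precision. The third does not dispose of it: the article does not leave the analysis open but names both the model and the contrast, so this concerns a stated choice.

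The size of the gain is also open to challenge. It rests on an undocumented ρ and on equal SDs, it shrinks when ρ is near 0.9 or all four readings are averaged, and it starts from about 88% power if the one-sided test is taken literally. All of that stands, which is why the result is given as a range.

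The documents do not support several stronger readings that a reader might infer:

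- *That the plan ignores baseline.* Both pre-acupuncture scores enter the ANOVA, and the contrast uses changes. The baseline is used, though inefficiently.
- *That chance imbalance in baseline pain passes straight into the result.* Only 1 minus the regression slope of it does. Two arms of 27 can differ by 1.96 × √(2/27) = 0.53 SD within chance; at ρ = 0.5 with equal SDs about half of that, 0.27 SD, reaches the change-score comparison. Its standard error already allows for this.
- *That the NRS will be transformed off its point scale, or contains many zeros.* The remark "Skewed data distribution will be normalized" is a general one for clinical data and does not name the NRS. No passage gives the distribution of scores.

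**Conclusion.** The point holds as one of efficiency. The written NRS analysis is valid and consistent with its sample size, but it gives up precision that the trial's own pre-acupuncture NRS could supply. If SD 2 is the SD of change and pre and post SDs are equal, the variance falls by 35% to 5% as the assumed ρ runs from 0.3 to 0.9, and two-sided power at 27 per arm rises from about 80% to between 93% and 82%. With unequal SDs at ρ = 0.5 the reduction could be about 9% or about 53%. The direction of the gain is secure apart from one degree of freedom; its size is not known from the document. A reader should not conclude that the planned analysis is biased or that 81 and 90 are wrong: neither follows.

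**What to change.** For the comparison before versus after acupuncture, prespecify as primary a linear model of the NRS taken after acupuncture and before the second scan, with group as factor and the NRS taken after the first scan as covariate. Report adjusted between-group differences in NRS points with 95% CIs.

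Keep the fatty-food-cue contrast as a separate planned comparison. For the between-group comparison of cue response after acupuncture, use the NRS after the second scan, likewise adjusted for the pre-acupuncture NRS.

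The cost is one degree of freedom and a change to the analysis text. The covariate is already collected and SPSS, the named software, fits the model. Trial status reports 6 participants recruited, so at that stage the change could still be fixed before outcome data are compared by group.

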In recent decades, the application of task fMRI makes it possible to provide evidence of human’s cerebral and behavioral response towards acupuncture stimulation [33–35]. Hence, in order to testify the hypothesis that either acupuncture with GB34 or EX-LE6 is superior in alleviating GSD patients’ symptoms compared to acupuncture with the non-acupoint, a fatty-food-cue task during MRI scan is designed to induce pain and accompanied discomforts of GSD patients and then the GSD patients’ behavioral and neural response change among all three groups before and after acupuncture will be compared. Therefore, the primary objective is to testify the therapeutic effect of acupuncture with GB34 and EX-LE6 in comparison to the non-acupoint and then further explore the superior effect between acupuncture with GB34 and EX-LE6 and finally investigate the potential central mechanism underlying acupuncture with GB34 and EX-LE6.

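### The planned NRS contrast is worded by time pairs, one-sided, and names no groups, so the acupoint versus non-acupoint test that is the primary objective is not specified

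*Protocol article*

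**What the plan says.** Under Primary outcome measurement: "The primary outcome will be measured by the NRS", taken at four timepoints. The Background gives the comparison of interest: "the primary objective is to testify the therapeutic effect of acupuncture with GB34 and EX-LE6 in comparison to the non-acupoint". The Sample size section anticipates "a reduction of NRS score by 2.4 points after acupuncture with GB34 or EX-LE6", while for the control "we anticipate a reduction by 0.85 points after acupuncture with non-acupoint". It adds "a standard deviation of 2" and concludes "we need at least 81 participants in total".

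Clinical outcome analysis has two steps. The first is a repeated-measures ANOVA of NRS over the four timepoints and three groups. The second is that "the planned contrast of changed NRS scores (before vs. after acupuncture; before vs. after fatty-food cues) will be conducted with a one-sided exact test", with p < 0.05 as the criterion. The second step fixes the time pairs, type of test, direction and threshold, but not the groups.

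The only pairwise group test that the Abstract names is a post hoc t-test of GB34 against EX-LE6. The Tukey or Bonferroni comparisons under In-scanner behavioral rating analysis apply to the food-desire ratings, not to NRS.

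**The concern.** Taken literally, the contrast asks whether NRS changed from one timepoint to another. Its null is no change over time. The trial's question is whether NRS fell more with an acupoint than with the non-acupoint, which is a different null. The protocol expects the first null to be false even in the control arm, where it anticipates a fall of 0.85 points.

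A fall within one arm mixes any acupoint-specific effect with non-specific needling effects, expectation, natural course and regression to the mean. Only the randomised difference between arms removes these. If a significant within-arm fall were reported as evidence for GB34 or EX-LE6, the conclusion on the primary outcome would not rest on randomisation. The direction adds to the doubt: a one-sided test suits a fall over time, whereas among three groups it has no direction until a pair of groups is named.

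**Working it through.** **Inputs.** From Sample size: fall of 2.4 points (acupoint) and 0.85 points (non-acupoint), SD 2, α = 0.05, power 0.80, 81 evaluable, 10% dropout to 30 per group. From Clinical outcome analysis: one-sided test, p < 0.05. *Assumption:* SD 2 is the SD of the change. The sample-size calculation implies this, but the text does not say it. A range is given in step 3.

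**1. Reproduce the plan's figure.** Two-group comparison of mean change, normal approximation:

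n per arm = 2 (z_α + z_β)² SD² / δ², with δ = 2.4 − 0.85 = 1.55.

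- Two-sided: 2 × (1.960 + 0.842)² × 4 / 2.4025 = 26.1, so 27 per arm and 3 × 27 = 81. This matches.
- Dropout: 27 / 0.9 = 30 per arm, 90 in total. This matches.
- One-sided: 2 × (1.645 + 0.842)² × 4 / 2.4025 = 20.6, so 21 per arm and 63 in total. This does not match.

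The trial was therefore sized for a two-sided comparison of change between one acupoint arm and the control arm.

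**2. Contrast run within an arm, acupoint no better than control.** True fall 0.85, SD of change 2, paired test, one-sided 0.05. Noncentrality = 0.85 / (2/√n).

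| n per arm | Noncentrality | Normal approx. | Paired t | Signed-rank (simulated) | At least one of two acupoints (t) |
|---|---|---|---|---|---|
| 27 | 2.21 | 0.71 | 0.69 | about 0.65 | 1 − (1 − 0.693)² = 0.91 |
| 30 | 2.33 | 0.75 | 0.74 | about 0.73 | 1 − (1 − 0.735)² = 0.93 |

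**3. If SD 2 is the SD of a single score.** SD of change = 2√(2(1 − ρ)), where ρ is an assumed pre/post correlation. Paired t, n = 27 to 30:

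| ρ | SD of change | Probability of significance per acupoint |
|---|---|---|
| 0 | 2.83 | 0.45–0.49 |
| 0.3 | 2.37 | 0.57–0.61 |
| 0.5 | 2.00 | 0.69–0.74 |
| 0.7 | 1.55 | 0.87–0.90 |

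**4. Contrast run between groups, same scenario.** With all three arms falling by 0.85, the one-sided 0.05 two-sample test of change rejects in 4.7% (n = 27) and 4.8% (n = 30) of 20,000 simulated trials.

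**5. Contrast counted only after a significant group-by-time test.** Approximating that test by an F test on the change at n = 27, a significant F together with a significant within-arm fall in at least one acupoint arm occurs in about 4.5% of trials.

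**6. Power of the between-group contrast at 2.4 versus 0.85 (t-based).** At 27 per arm: 80% two-sided, 88% one-sided. At 30 per arm: 84% and 91%. These are per contrast at 0.05, with no allowance for testing two acupoints.

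**The case against.** The best defence is that the sentence can be read as a between-group contrast. What it contrasts is already a change score, the parenthesis may only say which changes are meant, and it directly follows an ANOVA among three groups. The Background says that response change will be compared among the three groups, and the sample size is a two-group calculation. On that reading the error is about 5%. The article is also condensed, and the choice of group pairs is often left to the analysis plan.

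Much of this stands. A reader might infer that, on its own figures, the protocol's test declares a false effect about 70% of the time. The documents do not support that. The 70% is the power to detect a real 0.85-point fall, so rejecting no change would be correct. It becomes a false claim only if the contrast is run within arms and the result is presented as efficacy, and no section plans that inference. A reader might also infer that no randomised comparison of NRS is planned. That is wrong too, because the three-group ANOVA is written, and no section ranks the contrast above it.

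The defence does not settle the point. The ANOVA is an omnibus test over four timepoints and cannot say which acupoint beats the control. The contrast is not made conditional on it. The article also does not leave the contrast open: it fixes everything about it except the groups, and the one-sided direction does not match the two-sided sizing.

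**Conclusion.** The concern holds as a defect of specification. The planned NRS contrast names time pairs and no groups, is one-sided where the sizing was two-sided, and no section states the pairwise acupoint versus non-acupoint test that is the primary objective. The wording admits two analyses with very different consequences when an acupoint adds nothing over the control: about 5% false positives between groups, or about 69–74% significant results per acupoint if it is run within arms and read as efficacy. The second figure rests on a true fall of 0.85, 27–30 analysed per arm, a one-sided 0.05 paired t-test and SD 2 as the SD of change. It widens to about 45–90% if SD 2 is a single-score SD with correlation 0 to 0.7. The text does not establish that the within-arm analysis is intended.

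**What to change.** Replace the contrast sentence with one that names the groups, for example: *the planned contrasts are the differences between groups in NRS change from before to after acupuncture, GB34 minus non-acupoint and EX-LE6 minus non-acupoint, each two-sided at 0.05 with a 95% confidence interval.* Word the contrast for the change across the food cues in the same way. If an exact test is kept, permute group labels rather than before/after labels. Report within-arm before-after changes as descriptive only.

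The cost is a short change of analysis wording, with no new data or patients. Trial status reports 6 participants recruited, so it could be made early. The downside is that power at 27 per arm is about 80% two-sided rather than about 88% one-sided, and a within-arm fall can no longer support a conclusion.

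### No primary NRS contrast or group comparison is named and no error control is stated for the NRS contrasts; unadjusted one-sided testing gives a familywise error of about 9% to 24%, depending on which comparisons count

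*Protocol article*

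**What the plan says.** The NRS is the primary outcome. Under Primary outcome measurement, "The NRS will be assessed at four timepoints": before and after the first task scan (the second of these being just before needling), after acupuncture, and after the second task scan. No timepoint or change is singled out.

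Under Clinical outcome analysis, the four timepoints and three groups enter one repeated-measures ANOVA. The plan then adds "the planned contrast of changed NRS scores (before vs. after acupuncture; before vs. after fatty-food cues"), using a one-sided exact test at p < 0.05. It does not rank the two kinds of change, say which groups are compared, say which cue session is meant, adjust for multiplicity, or require a significant ANOVA first.

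The group comparisons appear elsewhere. The Background sets out "the hypothesis that either acupuncture with GB34 or EX-LE6 is superior in alleviating" symptoms relative to the non-acupoint. Its primary objective then names both points against the non-acupoint, followed by GB34 against EX-LE6. The abstract adds a post hoc t-test between the two points. Tukey or Bonferroni comparisons are named only for the in-scanner ratings, which are not the primary outcome.

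The Sample size section rests on one quantity: in a previous study the NRS "decreased by 2.4 points after acupuncture and by 0.85 points after non-acupoint acupuncture". From this, "With α = 0.05, 1 β = 0.8, and a standard deviation of 2, we need at least 81 participants in total", raised to 90 for dropout.

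**The concern.** The trial is sized for one comparison of one change score, but the analysis allows several, each significant at 0.05 in its own right. Two kinds of change combined with up to three group pairs give as many as six routes to a positive primary result. Because the hypothesis is worded so that success at one acupoint is enough, a false positive on any route could be reported as the trial's main finding.

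Sidedness adds to this. The contrasts are one-sided, whereas the stated sample size follows only from a two-sided test. A one-sided test also has no stated direction for GB34 against EX-LE6, since the plan does not predict which is better.

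**Working it through.** **Inputs from the Sample size section.** Reductions of 2.4 (either acupoint) and 0.85 (non-acupoint), so the difference is 2.4 − 0.85 = 1.55; SD 2; α 0.05 with sides not stated; power 80%; dropout 10%.

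**Reproducing the plan's figure.** n per arm = 2·SD²·(z₁ + z₂)² / Δ².
- Two-sided: 2 × 4 × (1.960 + 0.842)² / 1.55² = 26.1, so 27 per arm. 3 × 27 = 81, and 81 / 0.9 = 90. This matches.
- One-sided: 2 × 4 × (1.645 + 0.842)² / 1.55² = 20.6, so 21 per arm. 3 × 21 = 63, and 63 / 0.9 = 70. This does not match.

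The design is therefore one unadjusted, two-sided, pairwise comparison.

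**Error rate of the contrasts.** Assumptions not in the document:
- the stated SD of 2 is the SD of the change score;
- the correlation between timepoints is equal, at 0.5;
- t-tests stand in for the unspecified exact test;
- the pairs are A–C, B–C and A–B (A = GB34, B = EX-LE6, C = non-acupoint).

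For 27 per arm, no true effect and unadjusted one-sided 0.05, simulation (40,000 trials) gives these chances of at least one false positive:

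| Tests counted | Familywise error |
|---|---|
| A–C and B–C, acupuncture change | about 9% |
| plus A–C and B–C, second-cue change | about 17% |
| plus A–B on both changes | about 24% |
| same six tests, two-sided | about 21% |

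The one-sided figures take the cue test in the direction of benefit (a smaller rise in NRS). In the opposite direction the second and third rows become about 15% and 21%. Six independent tests would give 1 − 0.95⁶ = 26.5%. Varying the correlation from 0.3 to 0.8 hardly changes the results.

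**The proposed procedure.** A joint test of the three groups on the acupuncture change at two-sided 0.05, then the pairs at two-sided 0.05 only if it is significant:
- familywise error with no effect: about 5%;
- per-pair power: about 75–76%, against 80% without the joint test;
- power that both points beat the non-acupoint: about 68%, with or without the joint test.

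Under the one-sided test as written, power for both is about 80%, so the 68% belongs to two-sided testing only.

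**The case against.** The strongest reply is that the ANOVA comes first and the contrasts follow, so the plan already resembles an omnibus-then-contrasts procedure. If the contrasts were run only after a significant group-by-time interaction, the one-sided rate for the six tests would fall to about 3% when nothing works. This shows how much a gate would help, but none is stated. This gate would also not be enough. If only GB34 works, and its effect lasts to the final timepoint, the interaction is significant in about 95% of trials. At least one true-null contrast is then falsely positive in about 13–17% of trials.

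A second reply is that multiplicity detail often sits in an analysis plan that is not shown. That would excuse silence, but here the protocol itself fixes the significance rule for the primary outcome.

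Four stronger readings are tempting and are not supported:
- **That each of the four timepoints is tested at 0.05.** They enter one ANOVA; only the changes are contrasted.
- **That the plan lists three pairs for these contrasts.** The pairs are inferred, and A–B is described as a further exploration. Without it the range is about 9% to 17%.
- **That error is inflated and power falls short at the same time.** The first assumes that one winning point suffices, the second that both must win. The Background's hypothesis and objective point different ways, and one rule has to be chosen.
- **That the plan compares the pre-needling cue change between groups, or counts a within-group fall as success.** The text fixes neither.

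**Conclusion.** The concern holds in this form: the protocol sets a one-sided 0.05 rule for two kinds of NRS change without a primary contrast, a named group comparison, an adjustment or a gate, while its sample size is for one two-sided comparison. Followed as written, the chance of a false claim on the primary outcome is about 9% at the narrowest reasonable count, about 17% with the second-cue change added, and about 21–24% with all six tests. The document does not say which count applies, and the size of the inflation depends on it.

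The reproduction of 81 and 90 is exact. The error rates rest on the inferred pairs, t-tests in place of the exact test, an SD of 2 for change and equal correlation. The stated 80% is power for one comparison before any gate.

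**What to change.** 1. Name one primary contrast: the between-group difference in NRS change from just before to just after acupuncture, which is the quantity the sample size uses.
2. Test the three groups jointly on it at two-sided 0.05. Only if that is significant, test the pairs at two-sided 0.05. With exactly three groups this holds the familywise error at about 5%: once any two groups differ, at most one pair can be truly equal.
3. Make the cue contrasts secondary, and define the treatment-relevant one as the second-cue change minus the first-cue change, compared between groups. The first cue session precedes needling and serves as the reference.
4. Replace the one-sided test with a two-sided one, so that analysis and sample size agree.
5. State that 80% is power per comparison before gating, and that two-sided power for both points to beat the non-acupoint is about 68%. Say whether success needs one point or both.

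The cost is a change of wording and a fall in per-pair power from about 80% to about 75–76%, with no added patients. For comparison, Bonferroni over three pairs at 80% power would need 35 per arm, or 105 in total, and 105 / 0.9 = 117 with dropout. The Trial status section reports 6 participants recruited, so the amendment was still possible at an early stage.
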